### Sample size

The targeted sample size of 300 was determined using a formula, as illustrated below, for estimating sample sizes for binomial proportions. This calculation was based on a desired 95% confidence level, a 5% margin of error, and an assumed seroconversion rate of 75%. The result indicates a minimum sample size of 288 subjects required to accurately estimate the proportion of subjects achieving seroconversion. With this determined sample size, the lower limit of the 95% confidence interval is equal to or exceeds 70%.

$$n = \frac{Z^2 \cdot p \cdot (1-p)}{E^2}$$

Where:

- $n$  is the required sample size.
- $Z$  is the Z-score corresponding to the desired confidence level.
- $p$  is the assumed proportion of seroconversion.
- $E$  is the margin of error."

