### Study hypothesis

It is expected that a two-dose avian influenza vaccination schedule will induce **seroprotection** in at least 70% of the vaccinees (the lower bound of the two-sided 95% CI for the percent of subjects achieving seroconversion meets or exceeds 70%). The criterion for seroprotection is titer value  $\geq 80$  as analyzed by microneutralization test (MNT).

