## Study design

This is a prospective phase IV clinical trial for evaluating the humoral and cell-mediated immune responses in population groups to be vaccinated with the avian influenza vaccine according to the national recommendations in Finland.

The study is observational in nature as no vaccines are allocated or administered through this study protocol. However, blood and saliva samples are obtained to evaluate vaccine immunogenicity, and thus, the study is defined as an intervention study according to the EU regulation on clinical trials (536/2014). In the study, only licensed vaccines given within the framework of the national vaccination program/campaign are monitored, which have been given in accordance with the national vaccination campaign. In addition, the blood and saliva samples collected in the study do not pose more than minimal additional risk or burden to the safety of the subjects compared to normal clinical practice. Therefore, this study is a low-intervention trial. No control arm is included in this study.

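### The sample size section says the 95% lower limit will reach 70%, but at the assumed rate of 75% this happens only about half the time

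*Protocol*

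**What the plan says.** The Sample size section of the protocol uses n = Z²·p·(1−p)/E², a formula "for estimating sample sizes for binomial proportions", with "a desired 95% confidence level, a 5% margin of error, and an assumed seroconversion rate of 75"%. It reports: "The result indicates a minimum sample size of 288 subjects required to accurately estimate the proportion of subjects achieving seroconversion". The recruitment target is 300. The section ends with an assurance: "With this determined sample size, the lower limit of the 95% confidence interval is equal to or exceeds 70"%.

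The Study hypothesis section turns that limit into the study's criterion: "the lower bound of the two-sided 95% CI for the percent of subjects achieving seroconversion meets or exceeds 70"%. The study has a single group (Study design: "No control arm is included in this study"), so this comparison with 70% is the only formal test of success in the protocol. No power or probability of meeting the criterion is stated.

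**The concern.** The formula contains a confidence level and a margin of error but no power term. It says how wide the interval is expected to be, not where its lower end will fall. The lower end depends on the observed rate, which varies by chance around the true rate. Subtracting the 5-point margin from the assumed 75% gives 70%, but this is the lower limit only when the observed rate equals the assumed one. The closing sentence turns that single case into a property of the sample size.

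The sentence concerns the trial's own pass criterion, and the section on reporting of results says the findings will inform vaccination policy. A reader who takes the assurance at face value would see a lower limit below 70% as evidence that the vaccine fell short of expectation. With the planned size, such a result is close to an even chance even if the vaccine performs exactly as planned.

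**Working it through.** **Inputs.** Assumed rate p = 0.75, margin E = 0.05, 95% confidence, n = 288 and target 300 (Sample size); two-sided 95% interval with lower limit at or above 70% (Study hypothesis).

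**1. The plan's own figure.** n = 1.96² × 0.75 × 0.25 / 0.05² = 288.12. The stated 288 reproduces; strictly it rounds up to 289.

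**2. Why the chance is near one half.** At n = 288 the standard error at 75% is √(0.75 × 0.25 / 288) = 0.0255, so the half-width is 1.96 × 0.0255 = 0.050. The gap between the assumed rate and the threshold is 0.75 − 0.70 = 0.05. In the normal approximation the power is Φ(0.05/0.0255 − 1.96) = Φ(0) = 50%. Setting the margin equal to this gap produces that result by construction.

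**3. Lower limit when the observed rate is exactly 75%.**

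| Observed | Wald | Wilson | Exact (Clopper-Pearson) |
|---|---|---|---|
| 216/288 | 69.999% | 69.7% | 69.6% |
| 225/300 | 70.1% | 69.8% | 69.7% |

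**4. Exact probability of meeting the criterion at a true rate of 75%.** For each n and interval, r is the smallest count whose lower limit is at least 70%. The probability is P(X ≥ r) with X ~ Binomial(n, 0.75).

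| n | Interval | r | Probability |
|---|---|---|---|
| 288 | Wald, Wilson | 217 | 47.7% |
| 288 | Exact | 218 | 42.3% |
| 300 | Wald | 225 | 53.1% |
| 300 | Wilson, exact | 226 | 47.8% |

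**5. Dependence on the true rate.** At n = 300 the probability is 78% to 81% at a true rate of 77% and 98% to 99% at 80%. At n = 288, 80% power needs a true rate of 77.2% to 77.6%, and 90% power needs 78.3% to 78.6%.

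**6. Size needed for conventional power at 75%.** For 80% power, about 590 to 660 subjects are needed, depending on the interval. The exact power curve is saw-toothed: it first reaches 80% at 590 (Wald), 625 (Wilson) or 633 (exact), and stays there from 619, 654 or 662.

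**7. Fewer evaluable subjects.** The target exceeds the computed minimum by 300 − 288 = 12 subjects (4% of 300). The protocol gives no dropout rate, so the following is an assumed range. With 270 evaluable, the half-width is 5.2 points and the probability at 75% is 39% to 50%. With 240, these become 5.5 points and 36% to 42%.

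**The case against.** The best reply is that the protocol never claims a power. It describes a precision calculation, the 288 is correct, and the last sentence can be read as the interval expected at the assumed rate (75 − 5 = 70). If the determined size means the target of 300, the Wald lower limit at 225/300 is indeed 70.1%. The coin-flip figure also holds only at a true 75%. The protocol cites microneutralization seroconversion rates of 65% to 93% for earlier vaccine strains, so the chance could be close to certainty at the upper end or close to zero at the lower end. Finally, this is a low-intervention study without a control group, and the hypothesis is phrased as an expectation.

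Part of this stands. No power figure is misstated, 300 is a defensible size for estimation, and the difference between 288 and 289 is rounding. The choice of interval and the definition of the evaluable set may properly be left to an SAP, which is not at hand, so they are not faults in themselves.

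The central point survives. The sentence carries no condition on the observed rate and concerns the same limit that the hypothesis uses as its criterion. Even on the charitable reading it holds only for the Wald interval at 300; Wilson and exact limits remain below 70%. The 75% is the protocol's own planning value, and the cited range extends below it, so a higher true rate cannot be presumed. An SAP could add detail but would not make the sentence true.

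**Conclusion.** The concern holds. The derivation of 288 is sound, but the conclusion drawn from it is wrong: at the assumed 75% the lower limit reaches 70% with probability 42% to 48% at n = 288 and 48% to 53% at n = 300. This is true for either reading of the determined size and for all three intervals examined. It rests on independent binomial responses, a true rate equal to the planning value and every subject being evaluable; losses would lower the probability further. The chance rises steeply with the true rate, so this is a false assurance at the planning value and does not show that the study will fail. The hypothesis section also mixes seroprotection and seroconversion. That is a separate matter and does not alter these figures.

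**What to change.** Replace the closing sentence of the Sample size section, for example with:

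> With 289 evaluable subjects, the expected half-width of the 95% confidence interval is 5 percentage points at a rate of 75%. Using a Wilson or exact interval, the probability that the lower limit is at least 70% is about 46% if the true rate is 75%, 82% if it is 77.5% and 91% if it is 78.5%.

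The same statement for 300 evaluable subjects would read 48%, 83% and 92%.

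In the same edit it would help to:

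- name the interval that decides the criterion, since the probabilities depend on it;
- say that the number counts evaluable subjects: for seroconversion, those with a pre-dose sample, two doses and the sample three weeks after the second dose;
- give the half-width for a smaller evaluable number, such as 5.3 points at 255 (an illustrative figure, not one from the protocol).

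The cost is wording only. Enrolment, visits and the estimate itself do not change. The stated property becomes less favourable, but readers can then interpret a lower limit just below 70% correctly. If the sponsor wants 80% power at a true rate of 75%, about 590 to 660 evaluable subjects would be needed; correcting the text does not require this.

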### Laboratory methods

Laboratory analyses on samples are carried out at THL or at partner laboratories in Finland, or in the European Union region or European Economic Area, or at WHO Collaborating Centre for Reference and Research on Influenza (London, UK) in which case cooperation is agreed upon in a separate agreement with THL.

### Assessment of humoral immunity against influenza

We will assess antibody-mediated immunity from serum samples using various methods. The most important serological assay is the microneutralization test (MNT), which measures the functionality of the antibodies and which we have used in previous studies of avian influenza vaccine responses [5]. In a previous study conducted by THL a MNT titer  $\geq 80$  was found to correspond to the value of the HI test  $\geq 405$ . Depending on the virus lineage under investigation, the functional activity of antibodies can also be assessed using the hemagglutination-inhibition (HI) assay. The concentration

of antigen-specific antibodies and antibody subclasses, as well as functional properties of the antibodies can be assessed with different methodologies.

### Assessment of cellular immunity against influenza

We will isolate peripheral mononuclear cells (PBMCs) from the blood samples and study cell-mediated immunity from the samples, especially the activation of T cell immune responses activated by different influenza virus lineages or antigens. Cellular immunity will be assessed from thawed PBMC samples after stimulation with influenza viruses or virus antigens in cell culture. Cytokine (IFN-gamma and others) responses will be assessed by measuring the concentration of secreted cytokines in the cell culture media with Luminex technology. Additionally, mRNA expression of cytokines and other factors (e.g. inflammatory mediators and transcription factors) are measured from specific cell populations enriched with magnetic cell separation or sorted with FACS Aria flow cytometer. The methods to analyze COVID vaccine induced CD4 and CD8 T cell responses were recently developed [12-14] and the methodology can relatively rapidly be transferred to analyze cell-mediated immunity against influenza vaccine induced immunity.

The samples will also be used to examine humoral and cellular immunity against other pathogens and vaccines of interest as well as innate immunity and inflammatory responses to these factors. The potential association of these responses with the responses against seasonal and avian influenza vaccines and viruses will be described.

The samples may also be used in the validation and development of new immunological assays.

### Data collection from registers and participants (Cohorts 1 and 2)

Information of the seasonal and avian influenza vaccinations and other vaccinations is collected from the national vaccination register from the time of the study and previous 5 years (part of the Register of Primary Health Care Visits, Avohilmo), so that the effect of previous vaccinations on the measured immune responses can be evaluated. The national infectious diseases registry will be utilized to verify participants' prior exposure to seasonal or avian influenza viruses or other microbes causing infectious diseases. Subjects are asked to answer the questions on the consent form.

### Safety monitoring

In the study, only licensed vaccines given within the framework of the national vaccination program/campaign are monitored, which have been given in accordance with the SPC or according to the national recommendation. Therefore, this study is a low-intervention trial.

The study subjects are requested to inform the research staff if they suspect a post-vaccination adverse event (following the zoonotic influenza vaccine) that differs from the usual local symptoms (swelling, pain or bruising at the injection site) or general symptoms (fever, muscle and headache, fatigue, irritability, malaise and chills). At every contact with the study subjects, the study staff will ask whether any potential adverse events have occurred. The study subjects are also requested to inform the study staff if they suspect adverse events related to the study procedure, which differ from the usual swelling, pain or bruising at the blood sampling site.

The investigators will evaluate whether the adverse events are serious and whether the event is related to avian influenza vaccination or any other study procedure. THL will report all serious adverse events related to study procedures and all suspected unexpected serious adverse reactions

(SUSAR) related to avian influenza vaccines to the regulatory authority within time limits required by EU regulation on clinical trials. The safety follow-up for each subject will start at enrolment and last 3 months after the last vaccine dose. For adverse events related to the study procedure, the follow-up will extend until the end of the study. Additionally, THL will provide Fimea with an annual report including all serious adverse events reported to it during the study with a short update on subject safety. Adverse events potentially related to vaccines in the Finnish national vaccination programs/campaign are primarily reported to and assessed by Fimea. If a suspected unexpected serious adverse reaction reported by a subject is unequivocally found in the copy of the adverse reaction register received by THL from Fimea, it is not reported again to Fimea.

## Quality management

- quality control of the paper CRFs and forms by THL staff at/before the data entry
- searching for discrepancies and impossible values in the study database
- risk-based monitoring by the sponsor

The study is carried out, data is produced, documented and reported according to the study design, good clinical practice (GCP) and up-to-date regulatory requirements.

The sponsor has established a systematic quality assurance plan, based on a risk assessment, which includes a monitoring plan. The operation and quality assurance of the study are based on written guidelines approved by the PI.

Study documentation will be maintained in a trial master file (TMF)

The study will follow the sponsor's internal quality guidelines: data management and archiving, data protection and security, contract management, and study specific SOPs.

Informed Consent Form (ICF) will be obtained from the study participants prior to any research activities; and the identity of the subject will be verified before the consent is obtained. Informed consent forms, withdrawals and protocol deviations are recorded in the THL electronic information system. Paper CRFs and forms are verified by THL study staff before data entry.

## Ethical considerations

No vaccines are given in the study. The only interventions are the additional diagnostic methods, i.e., data collection and blood sampling performed by trained professionals. Thus, the study procedures carry out only minimal risk or harm to the subjects. All subjects have given a written informed consent, as described in section 'Informed consent'. The study protocol will be sent to the Medicines Agency (Fimea) and the National medical research ethics committee (TUKIJA) for evaluation via the EU portal (CTIS) and the study will not start before their approval.

The participant does not benefit personally from the study. However, the study results add knowledge on preventing avian influenza by vaccination, which benefits especially the risk groups participating in the study. The information is also important in the current epidemiologic situation in Finland for planning prevention and mitigation of potential worldwide pandemic avian influenza.

## Data protection

THL is the controller of the study register. Data is processed in accordance with the EU Data Protection Regulation (2016/679) and the national data protection law (1050/2018). The study's data protection notice will be published on the study's website.

## Timing

The study will start when avian influenza vaccinations are planned to start, in 2024. The duration of the clinical phase of the study depends on whether follow-up is deemed necessary and feasible, a minimum of 1 year and a maximum of 10 years. Analyses of the samples are started immediately at the start of the study and analysis of the samples are continued even after the end of the clinical phase. The study material will be maintained at THL for 25 years after the clinical phase of the study.

## Reporting of the results

The results are reported both as scientific publications and by communicating to stakeholders and communicating in the form of bulletins. The results of this national post-marketing immunological vaccine study will play a pivotal role in informing critical decision-making processes related to public health and vaccination strategies. The gathered immunological data from this immunogenicity study will be analyzed to evaluate the vaccine's ability to generate humoral and cell-mediated immune responses and the potential protective immunity induced against different avian influenza A(H5N1) strains. Decision-makers, including health authorities and policymakers, will leverage these findings to refine vaccination policies, prioritize high-risk populations, and make informed adjustments to public health measures.

